## Methods

### Study design

This study is a participant- and assessor-blinded, randomised, cross-over clinical trial. The study population is healthy volunteers with a male:female ratio 1:1. Inclusion will continue until 30 volunteers have completed the study (See Table 1 for inclusion and exclusion criteria). The intervention is 2 h of GA. On each of two intervention days, the volunteer will be exposed to GA by either TIVA (propofol) or by a volatile agent (sevoflurane). Each volunteer will receive both types of GA during the study, the order being determined according to randomisation. Participants will be blinded to the type of GA. The assessment of outcome will be blinded during analysis.

**Table 1 Tab1:** Inclusion and exclusion criteria

**Inclusion criteria**	**Exclusion criteria**
• Age ≥ 18 and ≤ 35 years • Healthy individual • BMI ≥ 18 kg/m^2^ and ≤ 30 kg/m^2^ • Normal electrocardiogram (ECG) • Normal physical examination, including neurological examination, auscultation of the heart and lungs, and measurement of blood pressure and pulse • American Society of Anaesthesiologists (ASA) class 1 [44] • Mallampati I-II and simplified airway risk index (SARI) 0–2 (i.e. no indication of difficult intubation). See Tables 2 and 3 for details • Right-handed • Female participants must use safe contraceptives (hormonal or mechanical, including IUDs) • Speaks and understands Danish • Provides oral and written informed consent	• Contraindications to MRI (as described below) • Left-handedness or ambidexterity. • History of complications to general anaesthesia, including malignant hyperthermia • Family history of malignant hyperthermia • Known incident of malignant hyperthermia or any unexplained complication to general anaesthesia among close relatives • Allergy to any kind of medication or material to which the volunteer could be exposed during this study • History of serious illness • History of cancer, immune disease, autoimmune disease, chronic pain or psychiatric illness • History of neurological disease with permanent neurological deficits or ongoing neurodegeneration • Major trauma or head trauma with any symptoms present at the time of inclusion • Surgery less than 6 weeks prior to the study period • Infection (with fever) less than 2 weeks prior to or during the study sessions • Daily use of any medication (not counting contraceptives) • Consumed anti-depressants during the last 30 days before study days • Weekly intake of > 21 (for women > 14) units of alcohol • Heavy intake of caffeine (> 5 cups/day) • Smoking during the last 30 days before study days • Substance misuse (assessed by the investigator) • Pregnancy • Reflux or dyspepsia • Poor dental status or oral health • Expected or suspected difficult airway • Declines receiving information regarding accidental pathological findings during MRI scans of the brain • Cannot cooperate to tests • Otherwise judged unfit for participation by the investigator
	Exclusion criteria during the study (leading to withdrawal)
	• Any of the above-mentioned exclusion criteria • Major trauma or head trauma during the study period • Surgery during the study period • Infection (with fever) during the study period • Consumption of more than 3 units of alcohol within 24 h before each study day (intervention day or MRI scan day) • Consumed analgesics within 3 days before each study day • Consumed anti-histamines less than 48 h before each study day • Intake of caffeine 12 h prior to each study day • Smoking

*BMI* body mass index, *IUD* intrauterine contraceptive device, *MRI* magnetic resonance imaging

**Contraindications to MRI** Contraindications to MRI include the following: severe claustrophobia rendering the subject unable to undergo MRI without administration of one or more sedatives or anaesthetics, pacemaker implant, artificial heart valve, cochlear/stapes prosthetics, irremovable insulin pump, neurostimulator, metal clips from previous surgical procedures, other metallic foreign objects, shrapnel or shell splinter, the presence of intravascular catheters other than a peripheral intravenous catheter, shunts and drainage tubes

**Table 2 Tab2:** Mallampati classification

**Class**	**Visible parts by inspection of open mouth**
I	Soft palate, fauces, tonsillar pillars and uvula
II	Soft palate, fauces and uvula
III	Soft palate and base of uvula
IV	Soft palate invisible

**Table 3 Tab3:** Simplified Airway Risk Index (SARI)

**Parameter**	**0 Points**	**1 Point**	**2 Points**
1. Mouth opening	> 4 cm	< 4 cm	–
2. Thyromental distance	> 6.5 cm	6–6.5 cm	< 6.5 cm
3. Mallampati class	I or II	III	IV
4. Neck movement	> 90°	80–90°	< 80°
5. Underbite	Can protrude jaw	Cannot protrude jaw	–
6. Body weight	< 90 kg	90–110 kg	> 110 kg
7. Previous intubation history	No difficulty	Unsure or unknown	Known difficulty

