### Hypotheses

The hypotheses of this study are that:
Compared with baseline, GA by propofol or sevoflurane is associated with (a) focal micro-structural neuroplastic changes (volume and morphology), (b) changes in white-matter tracts and (c) changes in resting- state neuronal connectivity, as detected by MRIGeneral anaesthesia by sevoflurane is associated with more pronounced changes in neuroplasticity compared with GA by propofolCompared with baseline, GA using propofol or sevoflurane is associated with reduced self-rated well-being (increased fatigue and reduced general comfort) and executive cognitive functions; a more pronounced reduction is observed after sevoflurane compared with propofolThe presence and severity of structural MRI changes after GA are correlated to changes in cognitive performance as well as self-rated measures of fatigue and well-being

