#### Secondary outcomes

Differences in resting-state functional MRI (rsfMRI)Severity and characteristics of fatigue, as measured by Multidimensional Fatigue Inventory (MFI-20) [42]Cognitive function including attention, speed, and executive functions as measured by computer-based neuropsychological tests (Paced Auditory Serial Addition Test (PASAT), Test of Attentional Performance (TAP) and Conners Continuous Performance Test, 3rd edition (CPT3))Quality of Recovery – 15-item questionnaire (QoR) [43]Correlations between MRI findings as well as clinical outcomes as described above

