##### Post-intervention care

In the post-operative care unit, the volunteer will be continuously monitored with heart rate and SpO_2_, while blood pressure will be measured every 15 min. The volunteer will receive oxygen supplementation if needed. Monitoring, care, discharge and intake of food and drinks will adhere to DASAIM’s standard of post-operative care [49, 50]. The volunteers will be observed for at least 2 h. Then, cognitive testing and questionnaires will be repeated before MRI 2. After MRI 2 the volunteer will be allowed to leave the hospital, but will be instructed not to remain alone for the next 24 h as recommended by the American Society of Anaesthesiologists (ASA) [51].

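### Table 1 makes inability to do the cognitive tests a withdrawal criterion even after anaesthesia, so the loss of later data can depend on an outcome of the trial

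*Protocol article*

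**What the plan says.** All references are to the protocol article.

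- **Table 1, entry exclusions:** one item is "Cannot cooperate to tests".
- **Table 1, second block:** it is headed "Exclusion criteria during the study (leading to withdrawal" and its first item is "Any of the above-mentioned exclusion criteria". No entry criterion is exempted, and no time limit is given.
- **Secondary outcomes:** these include "Cognitive function including attention, speed, and executive functions as measured by computer-based neuropsychological tests".
- **Hypotheses, third item:** anaesthesia with either agent "is associated with reduced self-rated well-being (increased fatigue and reduced general comfort) and executive cognitive functions". The reduction is expected to be larger after sevoflurane.
- **Post-intervention care:** after at least 2 h of observation, "cognitive testing and questionnaires will be repeated before MRI 2". The two follow-up sections repeat the tests, questionnaires and MRI at 1 and 8 days.
- **Study design:** "Inclusion will continue until 30 volunteers have completed the study".
- **Missing data:** everyone with at least one study session is kept in the analysis set, and analyses use observed data. A sensitivity analysis under MAR or MNAR follows only if missingness is above 5% and Little's test is significant.
- **Adherence strategy and discontinuation of the study:** for a non-completer, an account is required of follow-up and of the data collected.

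**The concern.** Before exposure, excluding someone who cannot do the tests is sensible, because no usable data could come from that person. After exposure, the same observation is the extreme of the effect that the third hypothesis predicts. Carrying the criterion over unchanged lets the outcome decide who stays in the trial.

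The volunteers at risk of removal are those whose cognition was most affected. Three things would suffer:

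- **Change from baseline at later visits.** It would be estimated without those volunteers and would be biased towards no effect.
- **The primary MRI outcomes.** Their remaining scans would not be taken. If structural change goes with cognitive change, as the fourth hypothesis proposes, the missing scans are informative too, and the planned correlations lose their extreme values.
- **The cross-over contrast.** A withdrawal in session 1 removes the whole second period, and with it that volunteer's sevoflurane-propofol difference.

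**Working it through.** The article gives no rate of unperformable tests and no withdrawal rate, so it has no figure to reproduce on this point. The check is a reading of the text, followed by a count of what the clause removes and whether the stated safeguard would respond.

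**1. Does the withdrawal list operate after anaesthesia?** Yes. Its alcohol item applies before every study day and names MRI scan days alongside intervention days. The follow-up MRI scan days are the visits 1 and 8 days after anaesthesia, where the cognitive tests are repeated. The list is therefore not confined to the time before exposure, and neither is its carry-over item.

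**2. What does the clause itself remove?** Each session has four assessments (before anaesthesia, after it, at 1 day and at 8 days), so a volunteer has 4 × 2 = 8 test occasions and 8 MRI scans. Take a volunteer who cannot do the battery at the first post-anaesthesia test and is withdrawn then. That battery precedes MRI 2. The failed test has no score with or without the clause, so it is separated out.

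| Failure in | Test occasions missing | of which due to the clause | MRI scans lost to the clause |
|---|---|---|---|
| Session 1 | 7 of 8 | 6 | 7 of 8 |
| Session 2 | 3 of 8 | 2 | 3 of 8 |

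Without withdrawal, and if later visits can be done, the same volunteer misses 1 of 8 test occasions and no MRI scan.

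**3. Would the sensitivity analysis be triggered?** The article does not say how missingness is counted. I assume it is counted over all test occasions, with 30 completers plus k withdrawn volunteers:

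- Session 1 failures: 7k / [8 × (30 + k)]. For k = 1, 7/248 = 2.8%. For k = 2, 14/256 = 5.5%.
- Session 2 failures: 3k / [8 × (30 + k)]. For k = 1, 3/248 = 1.2%. For k = 4, 12/272 = 4.4%. For k = 5, 15/280 = 5.4%.

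One failure in session 1, or up to four in session 2, stays below 5%. Above 5%, Little's test must also be significant. With a handful of incomplete records it has little to work with, and it cannot detect dependence on the value that was never observed.

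**4. Does anything else retain these volunteers' data?** The analysis set keeps what was observed before withdrawal. It does not supply visits that never took place. Recruiting to 30 completers restores the number, but with volunteers who could do the tests.

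**The case against.** **The criterion may have been meant for screening only.** It stands among suitability judgements, and the article describes re-screening before anaesthesia on the intervention day and again before session 2. No section orders a check of test cooperation at the post-anaesthesia battery. That intention is plausible, but Table 1 does not state it, and step 1 shows that the same list is used after exposure. Even on this reading, inability in session 1 could count against entry to session 2.

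**The triggering situation is partly prevented.** The 2 h of observation is a minimum, adverse effects are treated and observed until they have gone, and severe nausea has its own treatment. This stands. It makes the event less likely, and zero cases is a realistic result.

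**Data are not deleted.** Earlier observations stay in the analysis, a conditional MAR/MNAR analysis exists, and the account required for non-completers suggests that some follow-up is contemplated. This also stands, within the limits shown in steps 3 and 4.

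**Two stronger readings are not supported.** A reader might assume some number of failures, each far below baseline, and calculate how much the mean fall is understated at the failed visit. That figure would measure the absent score, which is absent with or without the clause. How an unperformable test is scored is a detail that a full protocol or analysis plan may settle. A reader might also infer that the sevoflurane-propofol comparison is necessarily biased towards no effect. That requires more failures after sevoflurane, which is the trial's hypothesis and not a documented rate.

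**Conclusion.** The point holds as a defect in the wording of Table 1. Applied literally, the criterion makes withdrawal after anaesthesia depend on a secondary outcome, and its direct cost is the later assessments of the most affected volunteers. Per volunteer, beyond the failed test, that is six test occasions and seven MRI scans for a failure at the first post-anaesthesia battery of session 1, or two and three for session 2.

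The direction of bias in the change from baseline is towards no effect, provided that those volunteers would still have been worse than the rest at the later visits. The between-agent contrast is biased only if failures differ by agent. The overall size cannot be stated, because the article gives no rate and the rate may be low in this population. The count against the 5% trigger rests on the assumed eight occasions per volunteer and on counting missingness across all of them.

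The outcome hit directly is secondary. The primary MRI outcomes are reached through the scans that are not taken. With about 30 volunteers even one or two cases would be noticeable, and the correction is simple, so it should be made.

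**What to change.** In Table 1, limit the criterion on test cooperation to assessments before the first induction. After that, record inability to perform the tests, with its reason, as an outcome, and continue the scheduled MRI, test and questionnaire assessments. Any decision on a second anaesthetic stays with the existing safety rules, which this change does not touch.

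A worst-rank analysis of unperformable tests can be added as a sensitivity analysis. Its downside is that it treats drowsiness, nausea and unwillingness as the same degree of cognitive impairment, which is why the reason should be recorded and why it should not be the main analysis.

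The cost is one qualifying phrase in Table 1, one field in the eCRF, and an amendment reported through the channels named under Trial status. The number of anaesthetics given and the sample size do not change.

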##### Follow-up MRI scan day (+ 1 day)

One day after GA cognitive testing, questionnaires and MRI scans (MRI 3) will be repeated.

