##### Follow-up MRI scan day (+ 8 days)

Eight days (7–10) after GA cognitive testing, questionnaires and MRI scans (MRI 4) will be repeated once more.

### Study session 2

Study session 2 will be initiated no earlier than 4 weeks after study session 1 (4 weeks after the intervention day), to ensure a sufficient wash-out period. Before the initiation of study session 2, the volunteer will be re-screened to ensure eligibility for continued participation. Session 2 will be identical to session 1, except that general anaesthetic will be changed from propofol to sevoflurane or vice versa.

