##### Pain

During the study mild pain may arise, which can be treated with paracetamol 1000 mg. Severe pain will be registered as an adverse event (AE) and the cause will be analysed to prevent recurrence. The participant will be treated according to established guidelines for managing severe pain in the Department of Neuroanaesthesiology.

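### Analgesic use within 3 days of a study day leads to withdrawal, yet the protocol itself provides analgesics on a day followed by MRI 3; the conflict is unresolved and, if Table 1 is applied, may select the sample on recovery

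*Protocol article*

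**What the plan says.** In the protocol article, the second part of Table 1 (under Study design) is headed "Exclusion criteria during the study (leading to withdrawal" and includes "Consumed analgesics within 3 days before each study day". An alcohol criterion in the same list shows what counts as a study day: "within 24 h before each study day (intervention day or MRI scan day".

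The Pain section states: "During the study mild pain may arise, which can be treated with paracetamol 1000 mg". For severe pain it adds: "The participant will be treated according to established guidelines for managing severe pain in the Department of Neuroanaesthesiology". It says nothing about withdrawal. The neighbouring sections on allergy and on hypotension do state when a volunteer is withdrawn.

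On timing, the day +1 section says: "One day after GA cognitive testing, questionnaires and MRI scans (MRI 3) will be repeated". The later visit is described as: "Eight days (7–10) after GA cognitive testing, questionnaires and MRI scans (MRI 4) will be repeated once more".

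On numbers, Study design says: "Inclusion will continue until 30 volunteers have completed the study". The Missing data section puts everyone who took part in at least one session into the intention-to-treat analysis and uses the observed data. It adds a sensitivity analysis under a random or non-random missingness model only if missingness exceeds 5% and Little's test is significant.

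**The concern.** For a volunteer given an analgesic for pain on day 0, Table 1 says withdraw, while the Pain section treats the pain as a routine event with no consequence for participation. No exemption for analgesics that the protocol provides is printed, so staff cannot tell which rule governs.

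If Table 1 governs, withdrawal is triggered by an event after randomisation that is plausibly related to fatigue, quality of recovery and cognitive performance. Replacement then preserves the nominal number while changing who is in the sample: completers are those who needed no analgesic in the relevant window after either anaesthetic. A volunteer withdrawn in session 1 also never provides the within-person comparison of sevoflurane with propofol.

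If neither rule clearly governs, handling may vary from case to case. The section on adherence and discontinuation says that a volunteer may be excluded for a protocol violation, which leaves discretion. The principal investigator opens the allocation envelope and stays in close contact with volunteers, so that discretion could be used with knowledge of the agent.

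**Working it through.** **The plan's own figure.** The 30 completers match the grey-matter calculation in the section on correction for multiple comparisons (8% difference, SD 10%, two-sided alpha 0.025, power 80%). With the two-group normal formula, 2 × (2.241 + 0.842)² × (10/8)² = 29.7, rounded up to 30. This point does not alter that figure. Because enrolment runs to 30 completers, the issue is who completes, not how many.

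**Timeline, passages side by side.**

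1. An analgesic given for pain after anaesthesia on day 0 falls one day before MRI 3. MRI 3 is a study day and the window is 3 days, so the criterion is met.
2. The same dose falls 7 to 10 days before MRI 4, outside the window. The conflict sits at day +1, but a volunteer withdrawn there loses MRI 4 as well.
3. Each session has four scan visits (MRI 1 to 4), eight in all. Withdrawal after day 0 of session 1 loses MRI 3, MRI 4 and all four visits of session 2, which is 6 of 8. Withdrawal after day 0 of session 2 loses 2 of 8. MRI 1 and MRI 2 of the session concerned are kept.
4. Read literally, the rule catches everyone. The Background section on general anaesthesia describes remifentanil as an analgesic, and the Induction section gives it to every volunteer on day 0.

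**Illustration if Table 1 is applied to analgesics given for pain.** The protocol gives no rate of use. Let p be the share of sessions with an analgesic on day 0, the same in both sessions and independent between them. All values of p are assumptions.

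- Withdrawn at some point: 1 − (1 − p)²
- Enrolment needed for 30 completers: 30/(1 − p)²
- Scan visits missing: p × 6/8 + (1 − p) × p × 2/8

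| p | Withdrawn at some point | Of the first 30 | Enrolment for 30 completers | Scan visits missing |
|---|---|---|---|---|
| 5% | 10% | 3 | 34 | 4.9% |
| 10% | 19% | 6 | 38 | 10% |
| 20% | 36% | 11 | 47 | 19% |
| 30% | 51% | 15 | 62 | 28% |

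For p = 10%, the last column is 0.10 × 0.75 + 0.90 × 0.10 × 0.25 = 0.0975. At p = 5% it is 0.05 × 0.75 + 0.95 × 0.05 × 0.25 = 0.049. If missingness is counted in visits, this cause alone would then stay just under the plan's 5% threshold.

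**Possible shift in an outcome mean.** Suppose, as an extreme case, that the withdrawn share p in a session is exactly the worst-recovering share, and that recovery correlates ρ = 0.3 to 0.5 with the outcome (assumed). The mean among those retained shifts by ρ × φ(z_p)/(1 − p). For p = 10%, φ(z_p)/(1 − p) = 0.195, so the shift is 0.06 to 0.10 SD. For p = 20% it is 0.11 to 0.18 SD, and for p = 30% it is 0.15 to 0.25 SD. In this model equal rates for the two agents cancel in the between-agent contrast. Rates of 10% and 20% with ρ = 0.5 leave 0.5 × (0.350 − 0.195) = 0.08 SD.

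**The case against.** The strongest reply is that Table 1 was never meant to cover drugs given under the protocol. The criterion sits among things a volunteer does before a visit: alcohol, anti-histamines, caffeine, smoking. The allergy and hypotension sections state withdrawal where it is intended, and the Pain section does not. The literal rule would also withdraw every volunteer because of remifentanil, which cannot be the intention. This has force: an unwritten exemption is plausible, and the full protocol, which is not shown, may contain it. What remains is that the rules as printed conflict and the scope of any exemption is not stated.

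A reader might infer that volunteers with pain are in fact removed and that the sample is therefore selected for good recovery. The documents do not support that. The effect depends on Table 1 prevailing over the Pain section. Only volunteers who take an analgesic would be affected, not all who have pain. If the Pain section prevails, there is no such selection; instead some scans and tests follow an analgesic, with no handling stated in the article.

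The Missing data section also deserves credit. It keeps visits already collected and foresees a sensitivity analysis. It does not restore visits that were never made, however, and Little's test may miss selective loss in a trial of about 30.

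Finally, these are healthy volunteers without surgery, for whom the protocol says only that mild pain may arise, so use could be rare.

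**Conclusion.** The point holds as an explicit, unreconciled conflict between Table 1, the Pain section and the day +1 schedule. Its literal wording also conflicts with the remifentanil given at induction. Selection on recovery is a conditional consequence: it follows if Table 1 is applied to analgesics given for pain.

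The size is unknown. The range of 19% to 51% of volunteers withdrawn at some point, and about 10% to 28% of scan visits missing, rests on assumed use of 10% to 30% per session and on independence between a volunteer's two sessions. The shifts in outcome means rest on further assumptions and on an extreme form of selection. The argument concerns mainly the secondary outcomes QoR-15, MFI-20 and cognition. It does not establish bias in the primary T1-weighted and diffusion outcomes, and bias between the agents would require analgesic use or its handling to differ by agent.

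**What to change.** The clinical lead should reconcile Table 1, the Induction section, the Pain section and the day +1 schedule so that one written rule covers analgesics provided by the protocol and applies to every volunteer regardless of agent. Which rule that should be is not a matter for this review.

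The analysis should then follow the rule chosen:

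- In either case, record analgesic use by session, keep all data actually collected in the intention-to-treat set, and report withdrawals by agent and reason.
- If volunteers stay in, add a sensitivity analysis that excludes visits following analgesic use.
- If volunteers are withdrawn, add a sensitivity analysis for non-random loss that does not depend on a significant Little's test.

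The cost is a short clarification or amendment and one extra analysis.
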